### Study 2 Design: Second Phase Remote Dosing Regime

At the 7-month appointment, the patient will be unblinded and given the option to continue or start real vCR stimulation for 6 additional months followed by a 1-month pause in stimulation. During the 7 additional months, patients will be remotely monitored and instructed to stimulate for six additional months as needed with parameters set to 2 h a day (maximum daily dose) to 2 h a day three times a week (minimum weekly dose). In addition, long-term effects will be measured after a 1-month pause in stimulation following the 6 additional treatment months.

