## Abstract

Enhanced neuronal synchronization of the subthalamic nucleus (STN) is commonly found in PD patients and corresponds to decreased motor ability. Coordinated reset (CR) was developed to decouple synchronized states causing long lasting desynchronization of neural networks. Vibrotactile CR stimulation (vCR) was developed as non-invasive therapeutic that delivers gentle vibrations to the fingertips. A previous study has shown that vCR can desynchronize abnormal brain rhythms within the sensorimotor cortex of PD patients, corresponding to sustained motor relief after 3 months of daily treatment. To further develop vCR, we created a protocol that has two phases. Study 1, a double blinded randomized sham-controlled study, is designed to address motor and non-motor symptoms, sensorimotor integration, and potential calibration methods. Study 2 examines dosing effects of vCR using a remote study design. In Study 1, we will perform a 7-month double-blind sham-controlled study including 30 PD patients randomly placed into an active vCR or inactive (sham) vCR condition. Patients will receive stimulation for 4 h a day in 2-h blocks for 6 months followed by a 1-month pause in stimulation to assess long lasting effects. Our primary outcome measure is the Movement Disorders Society-Unified Parkinson's Disease Rating Scale (MDS-UPDRS) part III off medication after 6 months of treatment. Secondary measures include a freezing of gait (FOG) questionnaire, objective motor evaluations, sensorimotor electroencephalography (EEG) results, a vibratory temporal discrimination task (VTDT), non-motor symptom evaluations/tests such as sleep, smell, speech, quality of life measurements and Levodopa Equivalent Daily Dose (LEDD). Patients will be evaluated at baseline, 3, 6, and 7 months. In the second, unblinded study phase (Study 2), all patients will be given the option to receive active vCR stimulation at a reduced dose for an additional 6 months remotely. The remote MDS-UPDRS part III off medication will be our primary outcome measure. Secondary measures include sleep, quality of life, objective motor evaluations, FOG and LEDD. Patients will be evaluated in the same time periods as the first study. Results from this study will provide clinical efficacy of vCR and help validate our investigational vibrotactile device for the purpose of obtaining FDA clearance.

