### Study Personnel and Their Roles

This study will include five movement disorders neurologists who are blinded during the first study. The first movement disorders specialist will serve as the *treating movement disorders neurologist* and perform physical and neurological examinations, evaluate and provide medical advice regarding patients' medication intake and serve as point of contact in the event of a serious or adverse event either unrelated or related to vCR for both the first and second study. The second movement disorders neurologist will serve as the studies' *main MDS-UPDRS movement disorders evaluator* who will perform assessments on patients throughout the first and second study. Three other movement disorders specialists will serve as the study's *video MDS-UPDRS III raters* for the first (main) study. The clinical research coordinators will oversee consent, objective motor measurements, video recordings, patient contact, vibrotactile glove administration, EEG recordings, voice recordings, and all self-report tests and questionnaires in both studies. Speech analysis will be performed by a voice disorders specialist and her trained team. An un-blinded statistical analyst, who is not associated with the study team and does not report to any member of the study team, will perform all statistical tests on outcome measures. All movement disorders specialists, speech analysis, and clinical research coordinators, will be blinded until completion of the first study.

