### Study 1 Design: Main Phase—Double Blind Sham-Controlled

We will perform a 7-month, double-blind, sham-controlled study including 30 PD patients randomly placed into either active vCR (*n* = 15) or a sham (*n* = 15) condition. All personnel and PD patients will be completely blinded to which stimulation pattern patients obtain. Parkinson's patients will receive vCR or sham stimulation for a total of 4 h a day (2 times 2 h a day with a break in between the 2-h sessions) at home for 6 months. To measure long-term effects, patients will pause stimulation for 1 month after the 6-month follow-up appointment.

#### Assessments: Study 1

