The following outcome measures and their descriptions will be administered to patients. The *MDS-UPDRS parts IA, IB, II, III*, and *IV* (29). The MDS-UPDRS parts IA and IB concerns non-motor experiences of daily living, in which IA is assessed by the study's main MDS-UPDRS movement disorders evaluator and IB is self-reported. Part II is motor experiences of daily living and is self-reported. Part III is the in-person motor evaluation assessed by the study's main MDS-UPDRS movement disorders evaluator. In addition, part III will be video recorded and sent to the three blinded video MDS-UPDRS III raters. Patient recordings will be evaluated after each patient completes his or her 7-month visit. Video raters will additionally be blinded to the date of administration. Part IV incorporates patient details on motor complications with the study's main MDS-UPDRS movement disorders evaluators observations and judgements. The *PD Quality of Life Questionnaire-39* (*PDQ-39*) (32) is a self-report questionnaire that examines health related difficulties specific to PD in eight quality of life categories within the last month. The *Parkinson's disease sleep scale* (*PDSS-2*) (33) examines PD related sleep issues during the past week. The *University of Pennsylvania Smell Identification Test* (*UPSIT*) (34) is a smell test comprised of 40 odors, in which patients try to correctly identify the odorant presented. Patients will also take a tolerability and usability questionnaire regarding the vCR device. We will perform a *vibratory temporal discrimination task* (*VTDT*) that consists of two vibratory bursts, with one burst delivered to the index finger and one burst to the middle finger. Each burst will start randomly on either the index or middle finger. This procedure will be performed on the right and left hand separately. The patient is instructed to judge if he/she felt a delay between the two vibratory bursts. This task was designed as a possible calibration method for future vCR studies by serving as a sensitivity measure for vibratory temporal changes, in which reduced perceived vibratory time differences correspond to increased vibratory temporal discrimination. Patients will also undergo clinically established *speech and voice assessments*. Speech samples will be collected at a sampling rate of 44,100 Hz on a laptop using the Praat Speech Analysis program (Version 5.4, University of Amsterdam). To collect samples, a head-worn, unidirectional microphone will be placed over the participant's ears and the microphone will be adjusted so that it is 6 cm from the participant's mouth. Specific samples will include sustained vowel phonations, sentence and paragraph length reading passages, and spontaneous speech. From these samples, speech and voice assessments will be conducted including measures of articulatory precision, speech intelligibility, speech rate, auditory-perceptual ratings of voice, and acoustic measures of vocal fundamental frequency, vocal intensity, and fundamental frequency and intensity variability. Additionally, the sentence intelligibility portion of the Assessment of Intelligibility in Dysarthric Speech (AIDS) (35) and patient self-assessment scales of Communicative Participation Item Bank (CPIB) (36) and the voice handicap index (VHI) (37) will be collected. For objective measures, patients will perform the *Kinesia ONE* motor evaluation, which uses a wearable accelerometer to assess motor activities similar to the MDS-UPDRS III and record their Parkinson's medication intake. The *Ambulatory Parkinson's Disease Monitoring* (*APDM*)'s Mobility Lab system will be used to measure objective gait disturbances. Lastly, the patient will also complete three different types of tasks during which *EEG* will be recorded. The first is a *sensorimotor EEG task*, in which patients receive a single vibratory stimulus to a random finger (excluding the thumb) on their non-dominant hand and are instructed with their dominant hand to push the response pad as fast as possible when they feel the vibratory burst. Each finger receives an equal number of vibratory pulses (50 per finger, equaling 200 trials) in a randomized order. Cortically, we expect to look at motor evoked potentials in response to cued vibration and their amplitude and latency changes throughout the course of treatment. Reaction time will also be documented. Additionally, we will record *vibration-only evoked potentials* in which we look at how two different types of vibratory pulses (high- and low- amplitude) affect different motor and sensory areas of the brain. The last task will be a recording done while the patient is at rest (*spontaneous EEG*). Patients will receive either active vCR or sham depending on the condition to which they were randomly assigned. For this task, we want to replicate our previous finding of decreased high beta band power (21–30 Hz) (17) for patients who received real vCR and quantify differences in activated brain areas in response to sham or active vCR. The MDS-UPDRS III off medication will be used as our primary outcome measure. All other measures are considered secondary.

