#### Remote Study Procedures

If the patient chooses to remain in the study, the following procedures will take place remotely in the patient's home. After the 7-month follow-up in study 1, the patient will be reconsented sent home with the vibrotactile device equipped with active vCR. The patient will stimulate as needed and as instructed using the parameters described above. Patients will take the online the PDQ-39, MDS-UPDRS parts IB and II, PDSS, FOG, and the usability and tolerability questionnaire of the vCR device. Patients previously in the sham condition will be given the usability and tolerability questionnaire 1 week after they start active vCR. Patients will complete all online questionnaires 1–2 weeks before every remote study visit. The patient will also continue to use the Kinesia ONE device one to three times a week so staff can monitor motor ability and report LEDD. The treating movement disorders neurologist will call patients after 1 month of stimulation to ask questions regarding the patients' treatment. At-home follow-up motor evaluations will take place at 10, 13, and 14 months *via* video meeting with the study's main MDS-UPDRS movement disorders evaluator. The study's treating movement disorders neurologist will additionally accompany the video call to check in on the patient. Depending on the type of medication, patients will go off medication (12–48 h) for these evaluations and perform the Kinesia ONE motor evaluation and the remote administration of the MDS-UPDRS IA, III, and IV (38). The remote MDS-UPDRS III will be our primary outcome measure, while all other measures are considered secondary. After 6 months of establishing a dosing regime, the patient will undergo a 1-month pause in stimulation and take his or her final online questionnaires and remote motor evaluation. The patient will mail his or her vCR device back to Stanford and will be thanked for his or her participation. For a detailed schematic of Study 2 events see Figure 4.

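### Unblinding each patient at that patient's own month 7, with the same staff in both studies, conflicts with the promise that staff stay blinded until Study 1 is complete

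*Protocol article*

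**What the plan says.** Two passages promise a blind for the whole of Study 1. The Study 1 design section states: "All personnel and PD patients will be completely blinded to which stimulation pattern patients obtain". The section on study personnel adds: "All movement disorders specialists, speech analysis, and clinical research coordinators, will be blinded until completion of the first study".

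The Study 2 design section sets the time of disclosure: "At the 7-month appointment, the patient will be unblinded and given the option to continue or start real vCR stimulation". The Abstract also describes Study 2 as unblinded. Nothing in the article delays disclosure, or the start of Study 2, until the last patient has finished Study 1.

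The same people serve both studies. The personnel section describes the main evaluator as the person "who will perform assessments on patients throughout the first and second study". In Study 1, "Part III is the in-person motor evaluation assessed by the study's main MDS-UPDRS movement disorders evaluator". In Study 2, the evaluations at months 10, 13 and 14 take place by "video meeting with the study's main MDS-UPDRS movement disorders evaluator", and the treating neurologist joins the call. Coordinators handle patient contact and all questionnaires in both studies.

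One Study 2 step differs by former arm: "Patients previously in the sham condition will be given the usability and tolerability questionnaire 1 week after they start active vCR".

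**The concern.** The two statements hold together only if all patients reach month 7 at the same time, or if finishing Study 1 means each patient's own finish. Otherwise, from the first 7-month visit onward, some staff can know the arm of finished patients while they still rate, test or advise patients in Study 1.

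Study 1 is meant to show efficacy against sham with 15 patients per arm, on a scale scored by a rater. Staff who know which finished patients had which stimulation might connect patients' descriptions of the device, side effects or response with an arm, and so form expectations about those still in the trial. The article itself withholds the sham parameters to protect the blind, so it treats such knowledge as a threat. A blind lost in this way cannot be restored.

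**Working it through.** The plan gives no figure to reproduce on this point. The check has two parts: setting the passages side by side, and an illustrative count.

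**Who can learn the former arm, and how**

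- *Coordinators.* The 1-week usability and tolerability questionnaire in Study 2 goes to former sham patients, and coordinators oversee all questionnaires. Anyone who follows that instruction knows the arm. The route is direct.
- *Main evaluator and treating neurologist.* The text unblinds the patient and does not say that these two are told. All Study 2 patients receive active vCR, so no task of theirs needs the former arm. They can learn it from the patient at the treating neurologist's 1-month call or at the video visits. The route is indirect.
- *Three video raters.* They rate for Study 1 only, work from recordings and do not know the visit date. No route to them is described.

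**Does Study 1 overlap with Study 2?**

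No recruitment period is given, but two passages imply staggered entry. The interim analysis takes place when 16 of the 30 patients have reached month 3, and recordings are rated as each patient completes month 7. Further, if the interim re-sizing adds patients, they enter at trial month 3 or later. Their 6-month rating then falls at month 3 + 6 = 9 or later, after the first scheduled unblinding at month 7. That overlap needs no accrual assumption, only that patients are added.

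**Illustrative count**

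Assume even accrual over A months, with the first patient entering at month 0. A patient who enters at month t has the 6-month rating at t + 6.

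- After the first unblinding (month 7): t + 6 > 7, so t > 1, and the share is (A − 1)/A.
- After the evaluator's first Study 2 video (month 10): t + 6 > 10, so t > 4, and the share is (A − 4)/A, or 0 if A is 4 or less.

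| Accrual A (assumed) | After first unblinding | After evaluator's first Study 2 video |
|---|---|---|
| 3 months | 2/3 = 67% | 0% |
| 7 months | 6/7 = 86% | 3/7 = 43% |
| 14 months | 13/14 = 93% | 10/14 = 71% |

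A count with 30 evenly spaced patients agrees. With 6 months' accrual, 25 six-month ratings follow the first unblinding and 10 follow the first video; with 12 months, 27 and 20.

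The first clock suits the coordinators, whose extra questionnaire comes a week after the Study 2 start. The second suits the evaluator, whose first described contact with unblinded patients is the month-10 video.

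**The case against.** Four points can be made in the plan's defence.

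1. *Part III is also rated from video.* Three raters with no Study 2 role score the recordings. This stands. A reader might infer that the rater of the primary outcome is unblinded and the sham comparison therefore biased. The article does not support that, because it does not say whether the in-person or the video score is primary. The exposed measures are in-person part III, parts IA and IV, medication advice (hence LEDD) and coordinator-run tests.

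2. *Knowing a finished patient's arm does not reveal an ongoing patient's arm.* This largely stands. Carry-over is possible but not shown. The sham is not described, so nobody can tell from the article whether device descriptions separate the arms. A reader might also infer that the 15/15 split lets staff work out the remaining allocations. That needs a fixed total, and the plan calls 30 a starting number that may be recalculated.

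3. *Completion of the first study may mean each patient's own completion.* On that reading the literal contradiction disappears. The possible carry-over to ongoing patients remains, and the Study 1 statement that all personnel are completely blinded sits poorly with it.

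4. *A condensed article leaves unblinding logistics to the full protocol or procedures.* This is fair for who tells the patient, and for whether disclosure follows the month-7 assessments. It does not cover the sham-only questionnaire, which the article states outright. The Figure 4 footnote describes that questionnaire without limiting it to former sham patients, so the article is not consistent on this step.

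A patient's arm may also matter to the choice of entering Study 2. That is a real cost of later disclosure, and is counted under the fix.

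**Conclusion.** The point holds as a conflict between the staff-blinding promise on one side and the month-7 disclosure and sham-only questionnaire on the other. It is direct for the coordinators. For the main evaluator and the treating neurologist it is a risk, since no text says they are told the arm. The video ratings are largely protected.

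The size of any bias cannot be derived. The shares above rest on assumed even accrual and count ratings made after someone could have learned a finished patient's arm. They do not count ratings made with knowledge of the rated patient's own arm, so reading 67% to 93% as the share of biased primary ratings would be wrong. For the evaluator's own Study 2 contact the range is 0% to 71%, and it is nil if accrual is as short as about 3 months. The documents likewise do not support the conclusion that the double-blind claim fails for later patients.

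**What to change.** Reconcile the personnel section, the Study 2 design section and the remote procedures as follows.

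- Do not disclose the Study 1 arm to patients or study staff until the last Study 1 patient's 7-month visit is done and the Study 1 data, including video ratings, are locked.
- Offer every patient Study 2 with a device stated to be active, with the stimulation pattern loaded by staff not affiliated with the study.
- Give the 1-week usability and tolerability questionnaire to everyone, as the Figure 4 footnote can already be read.
- Name the blinded video ratings as the primary part III score, or at least as a sensitivity analysis.

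The cost is protocol and consent wording, plus one extra questionnaire for former active patients. Every Study 2 patient receives active vCR, so Study 2 can start without the former arm. The downsides are that patients learn their arm later and decide on Study 2 without knowing it, and that some may guess it from a change in sensation. If the sponsor prefers to keep disclosure at month 7, Study 2 follow-up would need staff who take no part in Study 1 ratings, and the personnel section should say so.

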#### Remote Study Procedures

If the patient chooses to remain in the study, the following procedures will take place remotely in the patient's home. After the 7-month follow-up in study 1, the patient will be reconsented sent home with the vibrotactile device equipped with active vCR. The patient will stimulate as needed and as instructed using the parameters described above. Patients will take the online the PDQ-39, MDS-UPDRS parts IB and II, PDSS, FOG, and the usability and tolerability questionnaire of the vCR device. Patients previously in the sham condition will be given the usability and tolerability questionnaire 1 week after they start active vCR. Patients will complete all online questionnaires 1–2 weeks before every remote study visit. The patient will also continue to use the Kinesia ONE device one to three times a week so staff can monitor motor ability and report LEDD. The treating movement disorders neurologist will call patients after 1 month of stimulation to ask questions regarding the patients' treatment. At-home follow-up motor evaluations will take place at 10, 13, and 14 months *via* video meeting with the study's main MDS-UPDRS movement disorders evaluator. The study's treating movement disorders neurologist will additionally accompany the video call to check in on the patient. Depending on the type of medication, patients will go off medication (12–48 h) for these evaluations and perform the Kinesia ONE motor evaluation and the remote administration of the MDS-UPDRS IA, III, and IV (38). The remote MDS-UPDRS III will be our primary outcome measure, while all other measures are considered secondary. After 6 months of establishing a dosing regime, the patient will undergo a 1-month pause in stimulation and take his or her final online questionnaires and remote motor evaluation. The patient will mail his or her vCR device back to Stanford and will be thanked for his or her participation. For a detailed schematic of Study 2 events see Figure 4.

**Figure 4 F4:**
[figure not shown]
Depicts study 2 remote procedures that detail vCR dosing techniques and clinical data obtained. At the 7-month in-person visit, patients will be reconsented and will be sent home with active vCR. Patients will be instructed to stimulate between 2 h a day (maximum) to 2 h three times a week (minimum) from months 7 to 13, report their LEDD amount and perform the Kinesia ONE motor assessment one to three times a week to monitor motor ability throughout the entire trial. One to two weeks before every remote study visit, patients take the following questionnaires: MDS-UPDRS IB, II, PDSS, FOG, PDQ-39, and the Usability/Tolerability vCR device questionnaire. Remote study visits occur at 10, 13 months, and after a 1 month (14th month) pause in stimulation to assess long-lasting effects. During these remote study visits, patients are off medication and the study's treating neurologist gathers medical history and the study's main movement disorders evaluator assesses the remote MDS-UPDRS III, IA, and IV. *The Usability/Tolerability questionnaire is performed 1 week after the start of therapy and then 1–2 weeks before every study visit.

#### Statistical Analysis Study 2

The 15 patients receiving real vCR for 4 h a day in study 1 will be compared to the 15 patients who switch to real vCR in study 2 (previous sham patients). A 2 (4 h of daily vCR stimulation vs. decreased vCR stimulation) by 4 (baseline, 3, 6, and 7 months) mixed factorial ANOVA will be done individually on the MDS-UPDRS I, II, III, IV, with ratings for part III comprising of only remote tasks, LEDD, PDQ-39, FOG, PDSS, and Kinesia ONE ratings.

We hope to see no significant differences in evaluations taken from individuals receiving 4 h of stimulation and individuals receiving reduced vCR stimulation. This may suggest that between 2 h a day to 2 h three times a week of therapy is sufficient to drastically improve PD symptoms.

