### Summary and Outlook

Our study protocol comprises two study phases: *Study 1* is a double blinded randomized sham-controlled proof-of-concept study which corresponds to a phase IIA trial of the pharmaceutical trial categorization (70). The goal of this study is to demonstrate clinical efficacy of vCR compared to sham stimulation. To ensure therapeutic dosage, in study 1 we will apply two times 2 h of vCR or sham stimulation per day, respectively. However, in one patient of our case studies, in total 2 h vCR per day were sufficient to cause pronounced therapeutic effects (17), indicating that a daily dose of 4 h may not be necessary.

*Study 2* aims to obtain knowledge of the therapeutic benefits of vCR stimulation at a reduced dosage regimen. To this end, sham patients from study 1 will be crossed over into active vCR for study 2, totaling 30 active patients for the dose finding study 2. All patients in study 2 will receive vCR at a dose ranging from 2 h a day (maximum daily dose) to 2 h a day three times a week (minimum weekly dose) for 6 months. Patients will select their actual weekly dose within this reduced dosage range depending on their individual needs, supposedly requiring less compliance and causing less interference with patients' day-to-day activities. Study 2 serves three purposes: (i) In the patients who received vCR in study 1, study 2 enables to collect data regarding safety, tolerability, and efficacy on a longer time scale by delivering vCR for in total 12 months instead of 6. (ii) Comparing the effects obtained in vCR patients in study 1 with the effects observed in the sham patients from study 1 crossing over to low-dose vCR in study 2 provides a dose finding comparison between low-dose and high-dose 6-month vCR therapy, similar to a phase IIB trial in terms of the pharmaceutical trial categories (70). (iii) In addition, in both patient groups (i.e., vCR vs. sham patients from study 1) therapeutic effects obtained in study 2 will be separately correlated with the integral amount of self-administered dose.

Depending on the results of studies 1 and 2, additional dose finding studies might be envisioned to further optimize and potentially reduce the dosing pattern as well as to further optimize the stimulation pattern, e.g., by increasing the temporal jitter of stimulus onsets used for noisy vCR (17).

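### Study 2 fixes its dose comparison at 15 versus 15, but entry is optional after unblinding, so these are maximum numbers and only the reduced-dose group is additionally self-selected

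*Protocol article*

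**What the plan says.** Study 1 has "30 PD patients randomly placed into either active vCR (*n* = 15) or a sham (*n* = 15) condition". Statistical Analysis Study 2 carries both arms forward whole. One group is "The 15 patients receiving real vCR for 4 h a day in study 1"; these "will be compared to the 15 patients who switch to real vCR in study 2 (previous sham patients". The method is a 2 by 4 mixed factorial ANOVA (baseline, 3, 6 and 7 months), with part III limited to remotely assessable items. The stated hope is for no significant differences between the dose groups. Summary and Outlook repeats the full carry-over: "sham patients from study 1 will be crossed over into active vCR for study 2, totaling 30 active patients".

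Three other places make participation a choice. The Abstract says "all patients will be given the option to receive active vCR stimulation at a reduced dose". Under Study 2 Design, at the 7-month appointment "the patient will be unblinded and given the option to continue or start real vCR stimulation for 6 additional months". Remote Study Procedures begins "If the patient chooses to remain in the study" and adds re-consent. The Study 2 motor evaluations take place at months 10, 13 and 14.

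**The concern.** Optional entry and fixed group sizes agree only if every former sham patient finishes Study 1, opts in and is followed to month 14. Otherwise the reduced-dose group is a subset formed by patients' own decisions, and the 4-h group has no matching step. The comparison is then no longer one between the two randomised arms, although Summary and Outlook likens it to a phase IIB dose-finding comparison. This would remain even if the dose were assigned, the rating mode were the same and the extension were blinded.

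At stake is the reading of Study 2. The plan would take the absence of a significant difference as a sign that the reduced dose may suffice. If patients who do poorly after the switch leave, the reduced-dose mean moves towards that reading. A smaller group also makes a non-significant result easier to obtain.

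**Working it through.** **1. What each group must pass to enter the ANOVA** (assuming its conventional form, which needs all four values):

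| Step | 4-h group | Reduced-dose group |
|---|---|---|
| Complete Study 1 to month 7 | yes | yes |
| Opt in after unblinding, re-consent | no | yes |
| Complete months 10, 13 and 14 | no | yes |

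The first row is common to both groups. The other two are the asymmetry.

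**2. The stated 15.** 30 × 1/2 = 15, the full sham arm. With uptake u and Study 2 retention r, and no Study 1 loss, the expected number is 15·u·r. The chance that all 15 remain is (u·r)^15, if patients act independently. The document gives neither u nor r, so these are assumptions:

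| u | r | Expected | Chance of all 15 |
|---|---|---|---|
| 1.0 | 1.0 | 15 | 1 |
| 0.9 | 1.0 | 13.5 | 0.21 |
| 0.9 | 0.9 | 12.2 | 0.04 |
| 0.8 | 0.9 | 10.8 | 0.007 |
| 0.7 | 0.8 | 8.4 | 0.0002 |

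**3. Precision.** The only sizing figure, in the Study 1 statistical section, is f = 0.42 at N = 30. It reproduces as a between-group effect over m = 4 visits, with within-patient correlation ρ = 0.5 and 80% power (both assumed): λ = f²·N·m / (1 + (m − 1)ρ) = 0.1764 × 30 × 4 / 2.5 = 8.47, which gives power 0.802. With the 4-h group held at 15, power at f = 0.42 is 0.751 with 12 former sham patients and 0.703 with 10. This f was set for sham versus active in Study 1, so it is only a yardstick here.

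**4. Possible shift from selection.** If a fraction p leaves, and the tendency to leave correlates ρₛ with a poor outcome, the mean of those who stay moves by ρₛ·φ(z_p)/(1 − p) SD. For 3 of 15, p = 0.2 and φ(z_p)/(1 − p) = 0.280/0.8 = 0.350.

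| Lost of 15 | ρₛ = 0.3 | ρₛ = 0.5 | ρₛ = 0.7 |
|---|---|---|---|
| 1 | 0.04 | 0.07 | 0.10 |
| 2 | 0.07 | 0.12 | 0.17 |
| 3 | 0.11 | 0.18 | 0.25 |
| 5 | 0.16 | 0.27 | 0.38 |

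Losses and correlations are assumed throughout. For scale, the standard error of the group difference at 15 versus 12 is √(1/15 + 1/12) = √0.15 = 0.39 SD.

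**5. What a model on all available visits can recover.** In simulations of 40,000 runs with n = 15 and 3 lost, leaving after month 10 depended on the observed month-10 change (correlation 0.7), and month 10 correlated 0.5 or 0.7 with month 13. Complete-case bias was 0.11 to 0.16 SD. An estimator using the earlier values had bias of about 0.00. Its single-group standard error was about the same with 3 lost (0.29 SD for both) and larger with 5 lost (0.34 against 0.31 SD). The near-zero bias follows from making departure depend only on an observed value. The simulation does not cover patients who decline at month 7.

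**The case against.** The strongest reply is that 15 and 30 are nominal. The article calls 30 a starting number, subject to recalculation at the interim, states the option openly in three places, and words its dose conclusion cautiously. All 15 could opt in and finish. That stands: the document does not show that the count will fall short, only that it is a ceiling.

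A reader might infer that the full randomised vCR arm is set against sham patients who finish. The named ANOVA does not support that, because a vCR patient missing month 3, 6 or 7 would also be dropped.

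A reader might also infer that the reduced-dose result must be biased in its own favour. Former sham patients choose at month 7, before any active stimulation, so benefit from the reduced dose cannot drive that choice. A favourable bias is plausible only for losses after the switch, and even there it is not established.

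The article does not itself prescribe complete-case deletion, and missing-data rules may sit in an analysis plan not shown. Their absence is not the point. The article does fix the groups and names a method whose usual form loses patients unequally.

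Finally, Summary and Outlook defines the comparison in sham patients who cross over. Scoring decliners as having no benefit would therefore measure uptake, not the effect of the dose. That stands, and no such analysis is proposed.

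**Conclusion.** The point holds in a limited form. The fixed 15 and 30 conflict with optional entry and should be read as maxima. Under the conventional mixed ANOVA, opt-in and losses from month 7 to month 14 fall only on the reduced-dose group, so that group is self-selected in a way the 4-h group is not.

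The size cannot be derived from the document. With 3 of 15 lost and a correlation of 0.3 to 0.7, the shift is about 0.1 to 0.25 SD, smaller than the standard error of the difference (about 0.39 SD). The direction is unknown at opt-in. After the switch it could plausibly favour the hoped-for absence of a difference. The conclusion assumes the ANOVA is run on patients with all four values. It concerns the Study 2 dose comparison and leaves the Study 1 primary result untouched.

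**What to change.** 1. In Statistical Analysis Study 2 and Summary and Outlook, state the sizes as up to 15 former sham patients and up to 30 active patients.
2. Replace the 2 by 4 ANOVA for the Study 2 comparison with a likelihood-based repeated-measures model using every available part III value scored on the remote items. Include the months 0 to 7 values of all former sham patients and any Study 2 visits of those who stop early. Describe the result as conditional on data missing at random.
3. Show how many decline or stop, by original arm, with their month-7 part III. If uptake is incomplete, limit the conclusion to patients who chose to cross over.

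Cost: wording and some programming, with no new visits, because the months 0 to 7 values are already collected. The stated sizes look less favourable and the standard error may be slightly larger. The model rests on missing at random and cannot by itself correct for decliners whose choice depends on an outcome never observed. Items 1 and 3 are needed alongside it for that reason.
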